#### Secondary outcomes

The first secondary outcome will be the treatment outcome. This will be measured by evaluating the quality of treatment, the effectiveness of the appliance in delivering torque and the improvement in dental attractiveness. The quality of the treatment result will principally be measured by assessing the occlusal outcome using the Peer Assessment Rating Index (PAR Index) from study models recorded at the start and end of treatment. The torque of the maxillary incisors will be used to evaluate the effectiveness of appliance in delivering effective torque by measuring the angle between the long axis of the central incisors and the maxillary base from lateral cephalograms towards the end of treatment. The improvement in the dental attractiveness of the patient will be calculated using the aesthetic component of the IOTN. This will be evaluated by comparing the patient rating to the attractiveness of his or her teeth before and after treatment.

The second secondary outcome will be the biological side effects of the treatment, as measured by the amount of OIIRR. OIIRR will be established from periapical radiographs recorded at nine months into active treatment. Patients who show evidence of marked OIIRR will be treated in accordance with current recommendations.

The third secondary outcome will be the patient’s perception of wearing the fixed orthodontic appliance and of treatment outcome. This will be recorded using a questionnaire (Smiles Better) at six months after the start of treatment. Patient perception of the of fixed appliance treatment outcome will be measured by comparing patients’ pre-treatment and after-treatment questionnaires.

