## Methods/Design

### Trial design

The current trial is a multicenter, two-arm, parallel group, randomized controlled trial (Figure 1) designed following the CONSORT guidelines [10]. Patients who give informed consent to participate in this study will be entered into the study database, which will be held on one of the computers within the Orthodontic Department at Dundee Dental Hospital and School. Each participating patient will be allocated the next available study number at the start of active treatment using a series of opaque envelopes containing the treatment group.

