### Data and records to be collected

The following standardized data will be recorded for the trial participants at three stages of orthodontic treatment. Before start of orthodontic treatment: full orthodontic diagnostic clinical assessment, orthodontically trimmed study models at the start of orthodontic treatment, IOTN (aesthetic component score), long-cone paralleling technique periapical radiographs of maxillary central incisors, lateral cephalometric radiographs recorded before the start of treatment and patient questionnaire (pre-treatment). During orthodontic treatment: treatment duration, number of appointments, dates of key stages in fixed appliance orthodontic treatment, number of fixed appliance components replaced during active treatment, patient questionnaires (Smiles Better) regarding their perception of the impact of treatment (completed by the patient at six months from the start of orthodontic treatment), long-cone paralleling technique periapical radiographs of maxillary incisors recorded at nine months after the start of orthodontic treatment using digital radiography and lateral cephalometric radiograph recorded before the completion of active treatment.

End of orthodontic treatment: orthodontically trimmed study models at the end of treatment, patient questionnaire (post-treatment) and IOTN (aesthetic component score).

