**Table 1 Tab1:** **Statistical tests**

Outcome measure		Type of variable	Statistical test ***P***<0.05
**Primary outcome**	Duration of alignment stage for the upper and lower arches	Continuous, assuming normal distribution	One-way ANOVA test
**Secondary outcomes**	Number of visits required	Continuous, assuming normal distribution	One-way ANOVA test
	Occlusal outcome PAR	Continuous, assuming normal distribution	One-way ANOVA test
	Patient perception	Categorical data	Chi-square test
	Severity of OIIRR	Categorical data	Chi-square test or Friedman test

A list of statistical tests that will be used for data analysis depending on the type of data in the current trial. Peer Assessment Rating index (PAR), orthodontically induced inflammatory root resorption (OIIRR), analysis of variance (ANOVA).

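### Perceived treatment outcome is defined as a before/after comparison, but Table 1 gives all of patient perception one chi-square test with no stated contrast and no role for the baseline response

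*Protocol article*

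**What the plan says.** The Secondary outcomes section gives patient perception two parts.

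- **Wearing the appliance.** "This will be recorded using a questionnaire (Smiles Better) at six months after the start of treatment". This is a single measurement.
- **Result of treatment.** This part is measured by comparing the patient's "pre-treatment and after-treatment questionnaires".

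The section on data and records to be collected lists all three questionnaires: before treatment, at six months and at the end.

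The Statistical analysis section refers to Table 1 for the test planned for each variable. Table 1 has one row for both parts: "Patient perception Categorical data Chi-square test". The row names no time point, no contrast and no use of the pre-treatment response. Neither the response scale nor the number of items is described.

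The Trial design section describes a "multicenter, two-arm, parallel group, randomized controlled trial", so the randomized contrast is between arms.

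**The concern.** The definition and the test do not fit together. The definition makes the pre-treatment answer part of the outcome; the test as named gives it no place. A reader of Table 1 cannot tell whether before is compared with after or one arm with the other.

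The choice matters because the trial asks whether slot size changes perception. A before/after test asks whether treatment changes perception, which could happen equally in both arms. A between-arm test that leaves out baseline and ordering asks the right question but may do so with low sensitivity.

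The Background section hypothesizes no difference between the systems and includes patient perception among the outcomes concerned. Under that hypothesis an insensitive test is not a harmless choice: a missed difference would look like support for the expected conclusion.

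**Working it through.** **1. The plan's own figure.** The only powered outcome is treatment duration: a difference of 3 months, SD 7.2, two-sided 0.05, 80% power (Target sample size).

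- Normal approximation: n = 2 × (1.960 + 0.842)² × (7.2/3)² = 2 × 7.85 × 5.76 ≈ 90.4, so 91 per arm.
- Two-sample t-test: 91.4, so 92 per arm, with power 0.803 at 92.

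The stated 92 reproduces. It says nothing about power for questionnaire items, but it gives a sensible number of analysed patients for an illustration.

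**2. Why Pearson chi-square fails on before against after.** For one response category with share p at both times, the variance of the difference in proportions among n patients is 2p(1−p)(1−r)/n, where r is the within-patient correlation of the category indicators. Pearson chi-square uses 2p(1−p)/n. With r > 0 it overstates the variance and rejects too seldom. It also makes no comparison of the arms.

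**3. Simulation.** From the documents: 92 per arm and two-sided 0.05. Assumed, because the documents do not give them: a five-level ordered item made by cutting a normal variable so that baseline categories have equal shares; before/after correlation of 0 to 0.7; a common before-to-after shift of 0.4 SD in the between-arm runs; and, for power, a further 0.4 SD latent shift in one arm. There were 2,000 runs per setting. The Monte Carlo standard error is about √(0.05 × 0.95/2000) = 0.005 near the 5% level and about √(0.5 × 0.5/2000) = 0.011 near 50% power.

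Rejection rate with no true effect (nominal 0.05):

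| Correlation | Before vs after, one arm of 92, treated as independent | Between arms, post-treatment categories | Between arms, worse/same/better |
|---|---|---|---|
| 0 | 0.045 | 0.052 | 0.054 |
| 0.3 | 0.036 | 0.042 | 0.046 |
| 0.5 | 0.030 | 0.052 | 0.050 |
| 0.7 | 0.016 | 0.050 | 0.050 |

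Power for a 0.4 SD shift between arms:

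| Correlation | Chi-square, post-treatment | Chi-square, worse/same/better | Rank test, post-treatment | Baseline-adjusted score model |
|---|---|---|---|---|
| 0 | 0.482 | 0.269 | 0.701 | 0.704 |
| 0.3 | 0.476 | 0.342 | 0.696 | 0.727 |
| 0.5 | 0.478 | 0.420 | 0.692 | 0.784 |
| 0.7 | 0.464 | 0.564 | 0.704 | 0.873 |

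**4. Reading the tables.** Both between-arm chi-squares hold their level. Using the order of the categories adds 0.21 to 0.24 in power over the post-treatment chi-square (for example 0.704 − 0.464 = 0.240). Adjusting for baseline adds between almost nothing (0.704 − 0.701 = 0.003 at zero correlation) and 0.17 (0.873 − 0.704 = 0.169 at 0.7) over the rank test. The adjusted model is a linear model on category scores, used as a stand-in for an ordinal logistic model.

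**The case against.** The strongest reply is that nothing in Table 1 is actually wrong. The trial has two randomized arms and exists to compare them, so the natural reading is arm against arm, and that chi-square is valid. Baseline adjustment and item scoring are details that an article can leave to the full plan. The outcome is secondary and carries no power claim.

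Much of this stands, and it rules out several stronger conclusions that a reader might draw:

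- **That patient perception as a whole is a before/after measure.** It is not. The six-month questionnaire is a single measurement, and a between-arm chi-square on it is valid.
- **That the plan commits to chi-square on paired answers.** No section says so. The neighbouring root-resorption row does offer a related-samples test (Friedman) as an alternative, so the table does not keep the two kinds of contrast clearly apart; that shows ambiguity, not an error in the perception row.
- **That chi-square must be either invalid or blind to baseline.** Each patient's change could be classed as worse, same or better and compared between arms. That is valid and uses the baseline, at the cost of ordering and, in the illustration, with power of 0.27 to 0.56. The documents do not specify it.
- **That the aesthetic component is also assigned chi-square.** Its description, "This will be evaluated by comparing the patient rating to the attractiveness of his or her teeth before and after treatment", concerns measurement. Table 1 has no row for it.
- **That ordering is certainly lost.** The scale is not described; with yes/no or nominal items there is none to lose.

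The appeal to an unseen full plan does not settle the matter. The article does not leave the test open: it names one, for an outcome whose definition includes a baseline response that the named test does not visibly use.

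**Conclusion.** The point holds for perceived treatment outcome. Its definition is a before/after comparison, both questionnaires are collected, and the stated test gives neither the contrast nor a role for the baseline. Before against after, Pearson chi-square would be conservative (down to 0.016 against 0.05 at a correlation of 0.7) and would not compare the arms. Between arms on post-treatment answers it is valid but probably less sensitive than it need be: about 0.47, against 0.70 for a rank test and 0.70 to 0.87 with baseline adjustment.

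These powers are illustrative only. They depend on an assumed five-level ordered item, an assumed 0.4 SD shift and an assumed range of correlations, none of which comes from the documents. The advantage of ordering disappears if the items are unordered, and that of adjustment if before and after answers are nearly uncorrelated. This is a worthwhile improvement to a secondary analysis; it does not show that an invalid test is planned, and it does not touch the primary outcome.

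**What to change.** Split the patient-perception row of Table 1 in two.

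- **Perceived treatment outcome:** compare the arms on the post-treatment response, with arm and the pre-treatment response in the model. Use ordinal logistic regression if items are ordered, and binary or multinomial logistic regression otherwise.
- **Six-month Smiles Better questionnaire:** use a between-arm rank or ordinal test for ordered items, and keep chi-square for unordered ones.

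The cost is small: no new data, no change in sample size and no effect on the primary analysis. The sponsor must name the item or score to be modelled and its scale, which takes more than rewording one cell. The ordinal model adds a proportional-odds assumption, which can be checked.

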### Target sample size

The sample size calculation is based on the primary outcome of duration of orthodontic treatment. Using nQuery Advisor 7.0 sample size was calculated to detect a difference in mean treatment duration of three months (clinically important difference). Standard deviation was estimated using the studies of Amditis and Smith [5] and Eberting et al. [12]. A sample size of 92 in each group will have 80% power to detect a difference in means of three months assuming that the common standard deviation is 7.2 using a two group Student’s *t*-test with a 0.05 two-sided significance level. Assuming a 15 to 20% dropout rate, we will recruit a total of 216 patients.

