**Methods/Design:**

This is a prospective, multicenter, randomized clinical trial, undertaken in the secondary care hospital environment in the NHS Tayside region of Scotland (United Kingdom). A total of 216 orthodontic patients will be recruited in three centers in secondary care hospitals in NHS Tayside. The participants will be randomly allocated to treatment with either the 0.018-inch or 0.022-inch bracket slot systems (n = 108 for each group) using Victory series™ conventional pre-adjusted bracket systems (3 M Unitek, Monrovia, United States). Baseline records and outcome data collected during and at the end of orthodontic treatment will be assessed. The primary outcome measures will be the duration of orthodontic treatment in the maxillary and mandibular arches. The secondary outcome measures will be the number of scheduled appointments for orthodontic treatment in the maxillary and mandibular arches, treatment outcome using Peer Assessment Rating index (PAR), orthodontically induced inflammatory root resorption (as measured using periapical radiographs) and the patient’s perception of wearing orthodontic appliances.

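### The recruitment target of 216 allows for about 15% dropout, not the stated 15 to 20%; at 20% the power is about 77.5% instead of 80%

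*Protocol article*

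**What the plan says.** The section Target sample size of the protocol article bases the calculation on treatment duration. It aims to "detect a difference in mean treatment duration of three months (clinically important difference"), "assuming that the common standard deviation is 7.2", using a "two group Student’s *t*-test with a 0.05 two-sided significance level". The result is given as "A sample size of 92 in each group will have 80% power to detect a difference in means of three months". The next sentence turns this into the recruitment target: "Assuming a 15 to 20% dropout rate, we will recruit a total of 216 patients". The abstract (Methods/Design) repeats the total and gives the split as "n = 108 for each group".

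The section Intention-to-treat and imputation keeps every randomized participant in the analysis and fills a missing outcome with the median of the participant's own arm. Two sensitivity analyses use the 25th and 75th percentiles instead.

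**The concern.** Base size, dropout range and total stand together in one short paragraph. A reader will take 216 as the number that preserves 92 evaluable patients per group over the dropout range given. It does so only at about the lower limit, and the upper limit of 20% adds nothing to the target.

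This matters because the Background section hypothesizes no difference between the two slot sizes. If the result is not significant, readers will look to the planned power to judge how well the trial could have detected a three-month difference. That figure should hold at the less favourable end of the plan's own assumption, or the text should say that it does not. The upper end is also not far-fetched on the plan's own account: the Discussion expects treatment to last around two years and names patients moving away and missed records as sources of loss.

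**Working it through.** **Inputs** (all from Target sample size, except the per-group split, which is in the abstract): difference 3 months; SD 7.2; two-sided alpha 0.05; two-sample t-test; 92 per group evaluable; dropout 15 to 20%; 216 recruited, 108 per group.

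**1. The plan's base size.** Power comes from the noncentral t distribution with 2n - 2 degrees of freedom and noncentrality 3 / (7.2 × √(2/n)).
- n = 91: power 79.8%
- n = 92: noncentrality 3 / (7.2 × 0.1474) = 2.83, power 80.3%

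So 92 is the smallest whole number per group that reaches 80%. The stated figure reproduces.

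**2. Largest dropout that 216 can absorb.** 1 - 92/108 = 0.148, or 14.8%.

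**3. What remains of 108 per group, and the power.**

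| Dropout | Remaining per group | Power |
|---|---|---|
| 15% | 108 × 0.85 = 91.8 | 80.2% |
| 17.5% (midpoint) | 108 × 0.825 = 89.1 | 79.0% |
| 20% | 108 × 0.80 = 86.4 | 77.7% |
| 20%, whole patients | 86 | 77.5% |

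At n = 86 the noncentrality is 3 / (7.2 × 0.1525) = 2.73. The normal approximation gives 78.0 to 78.2% at 20%, so the choice of method hardly matters.

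**4. Recruitment needed to keep 92 per group**, as n / (1 - dropout).
- At 15%: 184/0.85 = 216.5, so 217 in total, or 218 if each arm is rounded up (92/0.85 = 108.2, so 109). That is one or two patients above 216.
- At 20%: 92/0.80 = 115 per group, 230 in total. That is 230 - 216 = 14 more, or 6.5% of 216.

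**5. Does the imputation rule repair the gap?** No. Giving each missing case its arm's median keeps the nominal count at 216 but adds no information about treatment duration, and it makes the variance look smaller than it is. The information for the comparison still comes from the patients with an observed outcome.

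**The case against.** The best defence is that the effect is small and the lower end is met. Both parts stand. At 15% the gap is a fraction of one patient per group and power is about 80%. At 20% the loss is about 2.5 points, which lies within the uncertainty of a planning SD taken from earlier studies. For illustration, with the full 92 per group an SD of 7.5 would give 77.0%, and with 86 per group an SD of 7.0 would give 79.8% (both SDs are assumptions, not figures from the protocol). It is also true that the protocol attaches 80% power to 92 per group and never says in so many words that 80% holds across the whole dropout range. That 216 was meant to protect the 92 over the range is the natural reading, but it is an inference.

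Three stronger readings are tempting, and the documents do not support them.
- *A wrong inflation formula was used.* A reader may notice that 184 × 1.175 = 216.2, which would be multiplication by one plus the midpoint dropout instead of division by one minus dropout. The protocol shows no formula and does not mention 17.5%. The correct division at 15% gives 216.5, which fits about as well. The two cannot be told apart, and the point does not depend on which was used.
- *The trial is seriously underpowered.* The figures in the table do not bear this out.
- *Covariate adjustment will make up the loss.* Table 1 lists one-way ANOVA for the continuous outcomes, with no covariates. Bringing 86 per group up to the equivalent of 92 would need baseline covariates that explain about 1 - 86/92 = 6.5% of the outcome variance, and the protocol gives nothing from which to judge that.

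What the defence does not remove is that 20% is the plan's own figure and the total does not allow for it.

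**Conclusion.** The point holds as a minor inconsistency in the sample size statement. The total of 216 is in effect an allowance for about 15% dropout, presented as one for 15 to 20%. At 20% the trial would have about 86 evaluable patients per group and about 77.5% power for a three-month difference, some 2.5 points below the stated level.

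This rests on the protocol's own difference, SD, alpha and test, on equal dropout in the two groups, and on reading dropout as loss of the primary outcome.

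**What to change.** Restate the last sentence of Target sample size along these lines:

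> 216 patients allow for about 15% dropout with 80% power; with 20% dropout (about 86 per group) power is about 78%.

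The alternative is to raise the target to 230, which keeps 92 per group at 20% dropout. For a loss of this size the restatement is enough, and it suits the stage of the trial, since Trial status expects the 216 to be reached in September 2014. The cost is one sentence and a slightly less favourable figure; nothing in the conduct or analysis changes.

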### Participant recruitment

Patients attending the orthodontic department in any of the trial centers for orthodontic treatment who meet the inclusion criteria will be assessed by the clinician planning the orthodontic treatment. The patients will be invited to participate in the study and will be given a participant’s and/or parents’ information sheet to take home with them. Patients will be asked to decide about joining the trial on the next appointment (after at least two weeks).

### Sequence generation and randomization

Simple randomization will be accomplished with no stratification using a restricted (10 number block) random number using http://www.graphpad.com/quickcalcs/randomn2.cfm to ensure equivalence of numbers in each group. The odd numbers will be allocated to group 1 and the even numbers to group 2. In every 10 number block from the random table, the sequence will be checked to ensure the even numbers are equal to the odd numbers. Each number in the random table will be given a study number and assigned into one of the study groups. A table for the allocation of the participants in the study will be composed and kept in a sealed envelope. All the documents used for the randomization and allocation sequence generation will be kept in a box in a locked office away from the clinical environments.

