### Participant allocation

Numbered, identical, opaque sealed envelopes will be used for patient allocation in the current trial. The allocation envelope contains the treatment allocation card showing either group 1 or group 2. The allocation envelopes will be kept in a labelled box in an agreed location in the clinical environments. After the clinician obtains informed consent from the patient, a dental nurse will be asked to identify the next allocation envelope in sequence. The allocation will only be revealed at the time of appliance placement. Then the allocation envelope will be opened in front of the participant. Both the participant and the clinician will be informed about the group allocation for the participant.

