### Ethics and dissemination

#### Ethics approval and consent

The study will be conducted in accordance with the principles of Good Clinical Practice. Approval was obtained from the East of Scotland Ethics Committee (approval number: 09/S1401/56) and National Health Service Tayside Research and Development (approval number: 20092E07). Any changes in research activity, except those necessary to remove an apparent, immediate hazard to the participant, will be reviewed and approved by one of the co-chief investigators. Amendments to the protocol will be submitted in writing to the East of Scotland Ethics Committee and Tayside National Health Service Research and Development.

Informed consent will be taken by the treating clinician (member of the research team) after clarifying any queries asked by the patient and/or the parents. In all trial sites, one of the trial team who is suitably trained will obtain consent from the participant and/or parent(s) or legal guardian(s). All research team clinicians will have had previous Good Clinical Practice training including obtaining informed consent. An independent clinician who is not part of the trial research group agreed to be an independent reference for participants and parents in case there are any further queries regarding the study. His contact information is included in the participant information sheet.

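### A single fixed block of ten, forced to 5:5, in an open-label trial could let up to about one allocation in six be deduced by someone who has seen the whole block

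*Protocol article*

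**What the plan says.** All references are to the protocol article.

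- **Sequence generation and randomization** describes the method as follows: "Simple randomization will be accomplished with no stratification using a restricted (10 number block) random number". It continues "The odd numbers will be allocated to group 1 and the even numbers to group 2", and then "In every 10 number block from the random table, the sequence will be checked to ensure the even numbers are equal to the odd numbers". Ten is the only block size named. The list is kept sealed in a locked office away from the clinics.
- **Participant allocation** uses numbered, opaque, sealed envelopes. On where they are held: "The allocation envelopes will be kept in a labelled box in an agreed location in the clinical environments". After consent a dental nurse identifies the next envelope in order. The arm is revealed at appliance placement, with the envelope opened in the participant's presence. Then: "Both the participant and the clinician will be informed about the group allocation for the participant".
- **Blinding** confirms that the clinician cannot be blinded after allocation and that the appliance type goes on a form in the case notes.
- **Participant inclusion criteria**, **Participant recruitment** and **Ethics approval and consent** have the operator who plans the treatment assess and invite the patient. Consent is taken by the treating clinician, who belongs to the research team.
- **Trial design** names three sites. The text does not say how the one unstratified sequence, or its envelopes, is divided among them.

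**The concern.** Sealing each envelope hides the single card. It does not hide the pattern that a fixed, balanced block imposes. Once one arm has used its five places, the rest of that block is determined. If blocks run from envelope 1, the envelope number gives the position in the block: 10, 20 and 30 each close one. The people who recruit also learn the earlier allocations.

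A clinician who can foresee the next arm could bring a case forward, hold it back or not put it forward. All malocclusion classes are eligible, with or without extractions, so patients can differ widely in complexity. The primary outcome is treatment duration. Steering of entry would therefore bear directly on the primary comparison, and no later analysis could fully remove it.

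The wording also contradicts itself: one procedure is called both simple and restricted to blocks. A reader cannot take both at face value.

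**Working it through.** **Plan's own figures.** The article gives no figure for predictability. The only related figures are 92 per group (difference 3 months, SD 7.2, two-sided 0.05, 80% power) and 216 recruited. Exact t-test power at 92 per group is 80.3%, and 184/0.85 = 217, close to 216. The point below does not affect the sample size.

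**Inputs.** Block size 10, split 5:5, two arms (Sequence generation and randomization); 216 patients (Target sample size); three sites (Trial design).

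**Step 1: forced allocations with a full view.** There are C(10,5) = 252 equally likely balanced blocks. After *i* allocations the next is forced if one arm already has five, with probability 2 × C(*i*,5)/252.

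| Position | Earlier allocations seen | Chance that it is forced |
|---|---|---|
| 1–5 | 0–4 | 0 |
| 6 | 5 | 2/252 = 0.8% |
| 7 | 6 | 12/252 = 4.8% |
| 8 | 7 | 42/252 = 16.7% |
| 9 | 8 | 112/252 = 44.4% |
| 10 | 9 | 252/252 = 100% |

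The sum is 420/252 = 1.667 per block, or 16.7%. Since 216 = 21 full blocks + 6, the total is 21 × 1.667 + 0.008 = 35.0, or 16.2% of 216.

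Positions 9 and 10 carry 1.444/1.667 = 87% of the forced allocations.

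**Step 2: best guess.** Guessing the arm with more places left, averaged over all 252 blocks, is right 65.3% of the time, against 50% by chance.

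**Step 3: partial view.** Suppose one sequence is shared by three sites and a clinician sees only local allocations. Simulation gives these shares of certain allocations. The site shares are assumptions, as the article gives none.

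| Assumed site shares | Certain allocations |
|---|---|
| 80/10/10 | 4.4% |
| 60/20/20 | 0.8% |
| equal thirds | 0.1% |

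With a full view but one earlier envelope drawn and not yet opened, the figure is 6.7%. With two it is 2.2%.

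**Step 4: effect of varied blocks.** Assume sizes 6, 8, 10 and 12 drawn with equal probability, and an observer who knows this set and sees every allocation. Simulated trials of 216 give about 1% certain allocations (0.9%) and a best-guess rate of about 66%. Certainty nearly disappears; the average guess rate does not fall.

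**The case against.** The strongest reply is that one in six is a ceiling that few people could reach. It needs one person who knows the block size and boundaries and has seen every earlier allocation in the block. With three sites and one sequence, a local view yields little (step 3). This stands, and the ceiling must be stated with its conditions.

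Timing also helps the plan. The patient decides at least two weeks after invitation. Recruitment of 216 over about 56 months (January 2010 to September 2014) means roughly 216/56 × 14/30.4 = 1.8 entries in two weeks, so block position is usually unknown at invitation. That weakens steering by invitation but leaves steering at consent or bonding. The nurse's role, the late reveal and the locked list are real safeguards, but they protect the card and the list rather than the pattern. The consent section also allows any suitably trained team member to take consent, so recruiter and treating clinician need not always be the same person.

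Some stronger readings are tempting but not supported:

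- *That one in six allocations were in fact foreseen.* The article does not say who knew the block size or how envelopes were divided. Whole blocks per site would restore the ceiling locally, but that is conjecture.
- *That the bias can be stated in months.* This needs an assumed size of steering, which the article does not give. It would also follow the guess rate, which the remedy does not lower.
- *That the odd/even check is invalid.* The generator's output is not described, and discarding and redrawing unbalanced blocks gives a valid permuted-block list.
- *That publication disclosed the block size.* Recruitment was near its end, so this could reach only late entrants.

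**Conclusion.** The concern holds as a moderate design weakness. The rule is stated in the article, so this is not detail left to a fuller document: one block size, forced to balance, in an open-label trial whose recruiters learn each allocation, with no stated masking of the block size.

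The size is at most about 35 of 216 allocations, given knowledge of the block size and boundaries and sight of the whole block. It is far less with a partial view. The ceiling is exact arithmetic; the partial-view figures rest on assumed site shares. The documents do not show that steering took place. The clash between simple and restricted randomization is a plain error of description.

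**What to change.** 1. **Envelopes not yet issued.** Replace the fixed block of ten with a computer-generated list using randomly varied block sizes (for example 6, 8, 10 and 12). Withhold the sizes from everyone who recruits or treats.
2. **Text.** In Sequence generation and randomization, replace simple randomization with blocked randomization. State how the envelopes were divided among the three sites and whether the block size was known to recruiters.
3. **Patients already entered.** Report the arm split by position within block and by centre. Add a sensitivity analysis of the primary outcome omitting the last positions of each block. Dropping positions 9 and 10 would omit up to 21 × 2 = 42 of 216 patients, so it is a check and not a replacement for the main analysis.

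Stratification by centre is not needed to meet this point.

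**Cost.** One new list and envelope set, a short amendment, and no extra patients or visits. The arms may end slightly unequal: an incomplete final block of 12 could leave a difference of up to 6. The present rule does not guarantee 108 per arm either, because 216 is not a multiple of ten. With the target enrolment expected in September 2014, the new list reaches only late entrants. For most patients the gain comes from items 2 and 3.
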